### Statistical analyses

All analyses will be conducted according to the intention-to-treat principle. Descriptive statistics will be generated to describe all sociodemographic and clinical characteristics, and outcome measures. To analyze whether randomization resulted in a balanced distribution of patient characteristics across the study arms, chi-square tests and independent samples t-tests will be used. When data is not normally distributed, Mann-Whitney U tests will be performed. In addition, independent samples t-tests will be used to test whether there are differences in outcome measures across study arms at baseline.

Linear Mixed Models (LMM) will be used to determine the efficacy of Oncokompas (e.g. changes in patient activation in the intervention group and the control group between t0, t1, and t2) by comparing longitudinal changes between both groups with fixed effects for study arm, time, and their two-way interaction, as well as a random intercept for subjects, and, if necessary, for referring hospitals. In case of baseline differences between study arms in sociodemographic and clinical characteristics, or outcome measures, the LMM analyses will be corrected for these differences. LMM will also be used to determine whether age, gender, socio-economic status (e.g. education level and work situation), cancer type, treatment modality, time since treatment, and baseline quality of life moderate the efficacy of Oncokompas. Fixed effects will be used for study arm, time, the potential moderator, and all two-way and three-way interaction effects, as well as a random intercept for subjects, and, if necessary, for referring hospitals.

Post-hoc analyses will be applied when significant results are found in the efficacy and moderation analyses mentioned above. Independent samples t-tests with Bonferroni correction will be used to measure the differences between the intervention group and the control group at follow-up measurements. To measure the effect sizes (ES) of the intervention, the (between group) Cohen’s d will be calculated. The magnitude of the ES is classified as large (≥ 0.80), moderate (0.50–0.79) or small (< 0.50) [39].

IBM Statistical Package for the Social Sciences (SPSS) version 26 (IBM Corp., Armonk, NY USA) will be used to perform all statistical analyses. All tests will be one-tailed. A *p*-value < 0.05 will be considered significant for all analyses.

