### Outcome assessment

The primary outcome measure to assess the efficacy of Oncokompas is patient activation. Secondary outcome measures are general self-efficacy and health-related quality of life. Also cost-utility outcomes will be evaluated. Outcome measures will be collected through online questionnaires at baseline (t0), two weeks after randomization (t1), and three months after the baseline measurement (t2).

An overview of the primary and secondary outcome measures is shown in Table 2.

**Table 2 Tab2:** Measurement overview

Aim	Outcome measures	Time point		
	*Instrument*	Baseline (t0)	Two weeks after randomization (t1)	Three months after baseline measurement (t2)
Efficacy				
*Primary outcome measure*	Patient Activation	X	X	X
	*Patient Activation Measure (PAM)*			
*Secondary outcome measures*	Self-efficacy	X	X	X
	*General Self-Efficacy Scale (GSE)*			
	Health-related quality of life	X	X	X
	*EORTC QLQ-C15 PAL*			
Cost-utility				
	Quality-adjusted life years	X		X
	*EuroQol 5 Dimensions (EQ-5D)*			
	Medical costs	X		X
	*iMTA Medical Consumption* * Questionnaire (iMCQ)*			
	Productivity costs	X		X
	*iMTA Productivity Cost Questionnaire (iPCQ)*			

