### Sample size

To demonstrate the presence of an effect on the PAM between t0 and t2 of at least 0.5 standard deviations as statistically significant in a one-tailed test at alpha = 0.05 and a power of (1 - beta) = 0.80, at least 51 participants in each condition will be required at three months follow-up. Anticipating a dropout rate of 25% between t0 and t2 (based on earlier research in this population [38]), 68 participants per condition arm need to be included at baseline (t0). In total, 136 cancer patients will be recruited for this study.

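### A subject random intercept assumes equal correlation over two weeks and three months; if correlation decays, the t0-t2 standard error is understated

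*Protocol article*

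**What the plan says.** The Statistical analyses section of the protocol article assesses efficacy with linear mixed models, "by comparing longitudinal changes between both groups with fixed effects for study arm, time, and their two-way interaction". For the dependence between a patient's repeated scores, the model contains only this: "as well as a random intercept for subjects, and, if necessary, for referring hospitals". The moderation models repeat the same random part. Neither description names a random slope or a residual covariance structure.

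Under Outcome assessment, the visits are baseline (t0), two weeks after randomisation (t1) and three months after baseline (t2). The gaps are therefore about 2, 11 and 13 weeks for t0-t1, t1-t2 and t0-t2.

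The Sample size section is built on this target: "presence of an effect on the PAM between t0 and t2 of at least 0.5 standard deviations". Its error rates are set "in a one-tailed test at alpha = 0.05 and a power of (1 - beta) = 0.80". The analysis section adds a general rule on sidedness: "All tests will be one-tailed". Bonferroni-corrected t-tests at follow-up come only after a significant mixed-model result.

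**The concern.** A subject random intercept with independent residuals is compound symmetry: one correlation for all three visit pairs and one variance for all visits. Here one pair is two weeks apart and another about three months apart, in patients with incurable cancer. Answers two weeks apart may well agree more closely than answers three months apart. The model would then average the three correlations and treat t0 and t2 as more alike than they are.

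The standard error of the t0-t2 change difference would be too small, and that of t0-t1 too large. The t0-t2 change is the quantity behind the sample size, so an error there would favour the intervention on the comparison that matters most. The mixed model also decides whether the follow-up t-tests are run at all.

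**Working it through.** **The plan's own figure.** For 0.5 SD, one-sided alpha 0.05 and power 0.80, the normal approximation is n = 2(1.645 + 0.842)²/0.5² = 49.5, so 50 per arm. The noncentral t gives power 0.799 at 50 and 0.806 at 51, which matches "at least 51 participants in each condition will be required at three months follow-up". Then 51/(1 − 0.25) = 68 per arm, 136 in total. The sample size reproduces. The check below concerns the analysis model only.

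**Inputs.** The model, visit times and powered effect come from the article. It gives no within-patient correlations and no visit-specific variances, so every correlation below is an assumption, written (r01, r12, r02).

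**Formula.** With equal variances σ², a change from t0 to t2 has variance 2σ²(1 − r02). With complete data, the random-intercept model estimates the residual variance as mean variance minus mean covariance, so it uses 2σ²(1 − r̄), where r̄ is the mean of the three correlations. Then:

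- SE ratio (model/true) for t0-t2 = √[(1 − r̄)/(1 − r02)]; for t0-t1, replace r02 by r01.
- One-sided type I error = P(Z > 1.645 × ratio).

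Example (.70, .60, .50): r̄ = 0.60, ratio = √(0.40/0.50) = 0.894, 1.645 × 0.894 = 1.471, error 7.1%.

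| Assumed (r01, r12, r02) | SE ratio t0-t2 | Error t0-t2 | SE ratio t0-t1 |
|---|---|---|---|
| .60, .60, .60 | 1.000 | 5.0% | 1.000 |
| .70, .62, .60 | 0.949 | 5.9% | 1.095 |
| .70, .65, .60 | 0.935 | 6.2% | 1.080 |
| .70, .60, .50 | 0.894 | 7.1% | 1.155 |
| .80, .65, .60 | 0.890 | 7.2% | 1.258 |
| .80, .60, .50 | 0.856 | 8.0% | 1.354 |
| .90, .60, .50 | 0.817 | 9.0% | 1.826 |
| .50, .70, .60 | 1.000 | 5.0% | 0.894 |
| .60, .75, .70 | 1.027 | 4.6% | 0.890 |
| .60, .60, .70 | 1.106 | 3.5% | 0.957 |

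In the last three rows r02 is not below the average, and the inflation vanishes or reverses. Those rows need the three-month pair to correlate more strongly than the two-week pair.

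**Smooth decay on the actual schedule.** Take correlation at a gap of w weeks as R(r02/R)^(w/13), with R the reliability. For R = 0.75 and r02 = 0.50 this gives (.705, .532, .500), ratio 0.918 and error 6.6%. Over R = 0.75 to 1 and r02 = 0.4 to 0.7, the error runs from 5.5% to 8.7%.

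**Unequal variances.** With all correlations 0.60, variances of (1, 1, 1.3), (1, 1, 0.8) and (1, 1.3, 1) at t0, t1 and t2 give 5.4%, 4.7% and 4.2%. Variance differences can therefore move the error either way.

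**Other forms of the test.** With time categorical, the 2-df arm-by-time test has a type I error of about 5.1-6.9% in the decaying scenarios, because the errors at t1 and t2 partly offset. With time linear in weeks 0, 2 and 13, the weights are (−5, −3, 8), with sum of squares 98. The model variance is 98(1 − r̄) and the true variance is 98 + 2(15r01 − 24r12 − 40r02). For (.70, .60, .50) these are 39.2 and 50.2, ratio 0.884, error 7.3%.

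**Simulation.** REML fits with 68 per arm and 25% monotone dropout (4000 runs each, Monte Carlo SE about 0.35 points) gave 5.5% under equal correlation, 6.4% for (.70, .62, .60), 7.3% for (.80, .65, .60), 8.1% for (.80, .60, .50), 9.9% for (.90, .60, .50) and 4.3% for (.60, .75, .70). The pattern agrees with the formula.

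**The case against.** A reader might infer that the t0-t2 standard error is too small and that the type I error exceeds 5%, as facts. The documents do not support that. They report no correlations or visit variances, and under equal correlation the model is correct. This objection stands and limits the point to a conditional one.

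A steep scenario can also overstate the size. The t1-t2 and t0-t2 gaps are about 11 and 13 weeks, so smooth decay makes their correlations nearly equal. A fall from 0.60 to 0.50 between them is hard to justify. This stands too: with r01 near 0.70 and r02 = 0.50, smooth decay gives 6.6%, not 7.1%.

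The article does not name t0-t2 as the decisive model contrast. An overall interaction test is only slightly inflated, and the follow-up t-tests do not use the mixed-model covariance. This stands in part. However, the trial is sized on t0-t2, and a 2-df test has no one-tailed form, so the one-tailed rule suggests a single contrast. The t-tests also depend on a significant mixed-model result.

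Finally, residual covariance is often left to an analysis plan, and SPSS mixed models allow one to be added. A plan not shown may do so, and confirming it would settle the matter. The point still concerns a stated structure: the article sets out the random part of the model twice, and both times it is an intercept.

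**Conclusion.** The point holds conditionally. As written, and with independent residuals, the model assumes equal correlation and equal variance over unequally spaced visits. If correlation decays with time, r02 is below the pooled value and the t0-t2 comparison becomes anti-conservative, with a one-sided type I error of roughly 5.5-9% by the formula. The most extreme simulated case with dropout reached 9.9%. The overall 2-df test is affected less, at about 5.1-6.9%, and the t0-t1 comparison becomes conservative.

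These sizes rest on assumed correlations and, except in the unequal-variance check, on equal variances. The mechanism is certain, the direction is plausible, and the size is unknown. The stated model is a weak choice for this schedule, but the documents do not show that the trial's p-value will be wrong.

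**What to change.** Replace the subject random intercept with an unstructured residual covariance over the three visits, in the efficacy and moderation models alike. Keep the hospital intercept if it is needed. Fit by REML with Satterthwaite or Kenward-Roger degrees of freedom where the software offers it. State in advance a simpler structure, such as heterogeneous autoregressive, for use only if the model does not converge. Name the t0-t2 arm difference in change as the decisive model contrast.

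SPSS MIXED can fit this through its REPEATED specification. The cost is a line of text and syntax and six covariance parameters in place of two (three variances and three correlations), from 136 patients. If the correlations are in fact equal, the analysis remains valid and only a little precision is given up.

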#### Randomization

After completion of the baseline questionnaire, patients are randomly assigned to the intervention group or the control group, using block randomization. Blocks will have a length of four up to eight. Randomization takes place in a 1:1 ratio. The randomization scheme is created by a researcher not involved in the study, which also carries out the allocation of participants, using random allocation software (i.e. Sealed Envelope). Subsequently, this researcher notifies the coordinating researcher of the study about the outcome of the allocation after randomizing a participant. Blinding of the coordinating researcher is not possible since this researcher will send out the invitations for Oncokompas to patients and has to support patients during the study, for example when they have questions regarding technical issues.

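### Baseline PAM is adjusted for only if a baseline test finds a difference, so a chance gap can shift the arm-by-time effect and precision is lost; always adjusting would cure both

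*Protocol article*

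**What the plan says.** The Statistical analyses section of the Protocol article describes a linear mixed model for PAM at t0, t1 and t2. Its fixed effects are arm, time and arm by time, with a random intercept per subject (and per referring hospital if necessary). Baseline PAM is thus one of the responses, and nothing constrains the arms to share a t0 mean.

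The same section compares patient characteristics between arms with chi-square tests, t-tests or Mann-Whitney U tests. For outcomes, "independent samples t-tests will be used to test whether there are differences in outcome measures across study arms at baseline". It then makes adjustment conditional: "In case of baseline differences between study arms in sociodemographic and clinical characteristics, or outcome measures, the LMM analyses will be corrected" for them. No adjustment covariate is fixed in advance, and the form in which a covariate would enter is not stated. For the moderator models, by contrast, the two-way and three-way interactions are spelled out. All tests are one-tailed at p < 0.05.

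The Sample size section targets "an effect on the PAM between t0 and t2 of at least 0.5 standard deviations", with a "one-tailed test at alpha = 0.05 and a power of (1 - beta) = 0.80", and concludes that "at least 51 participants in each condition will be required at three months follow-up".

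**The concern.** Every patient completes the baseline questionnaire before randomisation, so any baseline difference between arms is due to chance. A significance test is then a poor guide to which covariates matter. The usual reason to adjust for the baseline outcome is that it predicts the follow-up outcome, and that holds whether or not the arms happen to differ.

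Two things are at stake. First, with t0 PAM as a free response, the arm-by-time effect compares changes. An arm that starts low by chance tends to drift back up, and this regression to the mean is counted as part of the treatment effect. The plan's safeguard may act only on large gaps, or hardly at all. Second, baseline PAM carries information that would narrow the confidence interval, and the planned model does not use it fully.

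**Working it through.** **Inputs.** From Sample size: 0.5 SD, one-tailed 5%, power 80%, 51 per arm at t2, 25% dropout, 68 per arm at t0. From Randomization: "Randomization takes place in a 1:1 ratio". Assumed, because the documents give no value: the t0-t2 correlation rho, with 0.5 to 0.6 as the main range and 0.3 as a low case. PAM is in SD units, with equal variance at each visit.

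**1. The plan's own figure.** A one-sided two-sample t-test for 0.5 SD needs 50.15 per arm, so 51. Then 51 / 0.75 = 68, and 2 x 68 = 136. The sample size reproduces and is not in error.

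**2. Shift from a chance baseline gap.** The t2 arm-by-time effect is (gap at t2) - (gap at t0). Given a baseline gap D0 and no treatment effect, the expected t2 gap is rho x D0, so the shift is rho x D0 - D0 = -(1-rho) x D0.

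- Standard error of the baseline gap at 68 per arm: sqrt(2/68) = 0.171 SD.
- Expected absolute gap: sqrt(2/pi) x 0.171 = 0.14 SD. Shift: 0.055 SD (rho 0.6) to 0.07 SD (rho 0.5).
- Gap of 1.645 x 0.171 = 0.28 SD, reached in either direction about 10% of the time. Shift: 0.4 x 0.28 = 0.11 SD (rho 0.6) to 0.5 x 0.28 = 0.14 SD (rho 0.5).

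**3. Does the correction remove it?** Random-intercept models were fitted to 12 simulated data sets per scenario (68 per arm, three visits, rho 0.6, no treatment effect, baseline gap forced to +0.3 SD). Theory gives -0.4 x 0.3 = -0.12 SD. Mean t2 arm-by-time estimates in SD:

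| Model | Complete data | 25% dropout |
|---|---|---|
| As planned, no covariate | -0.125 | -0.105 |
| Plus an age-like main effect | -0.125 | -0.109 |
| Plus baseline PAM as main effect | -0.125 | -0.106 |
| Plus baseline PAM x time | -0.001 | 0.017 |
| Common t0 mean in both arms | -0.007 | 0.015 |
| t1 and t2 as outcomes, baseline PAM as covariate | -0.003 | 0.017 |

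With complete data, a main-effect covariate changes each estimate by no more than 3e-15, which is rounding error. With dropout the mean absolute change is 0.01 to 0.02 SD.

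**4. When would the trigger act?** At 68 per arm a PAM t-test is significant only beyond 1.645 x 0.171 = 0.28 SD (one-tailed) or 1.96 x 0.171 = 0.34 SD (two-tailed). Smaller gaps stay uncorrected under any form of correction.

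**5. How often would something trigger?** Seven characteristics are listed under Sociodemographic and medical data: 1 - 0.95^7 = 0.30. Adding PAM, GSE and the nine QLQ-C15-PAL scales makes 18 tests: 1 - 0.95^18 = 0.60. Both figures assume independent tests.

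**6. Precision.** The variance of the change form is proportional to 2(1-rho), and that of the baseline-adjusted form to 1-rho^2. The ratio is (1+rho)/2, which is 0.75 at rho 0.5 and 0.80 at rho 0.6. In the complete-data simulation the standard error fell from 0.151 to about 0.136.

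**7. Power at 51 per arm**, if 0.5 SD is a cross-sectional SD (one-sided 5%, normal approximation):

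| rho | Change form | Baseline-adjusted |
|---|---|---|
| 0.3 | 0.69 | 0.84 |
| 0.5 | 0.81 | 0.90 |
| 0.6 | 0.88 | 0.94 |

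Using the t distribution, the first entry is about 0.68.

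**The case against.** The strongest reply is that the article does not say how the correction enters the model. A baseline x time term, or moving t0 out of the responses, would remove most of the carry-over, and a fuller document may specify one. This stands. That the correction is inert is a conditional statement: exact for a main effect with complete data, and nearly true with the planned dropout. A main effect is the natural reading, because interactions are named for moderators and not here, but it remains an inference. What survives is that, whatever the form, correction depends on a test that misses gaps below 0.28 to 0.34 SD. The word significant is not in the sentence either, but the tests that precede it and the general p < 0.05 rule make significance the evident trigger.

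It is also fair that the two complaints partly offset each other. If the correction hardly moves the arm-by-time effect, then choosing covariates from the data does little harm to that estimate. The trigger rates in step 5 show how unstable the model specification is, not how large the bias is. Correlated scales would also make the true rate for 18 tests lower than 60%.

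A reader might infer from the blanket one-tailed rule that a gap in the other direction never triggers a correction. The documents do not support this. No direction is given for the baseline tests, they are described as looking for differences, and chi-square tests on several categories have no tail.

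A reader might also infer that the trial is underpowered. At rho 0.5 to 0.6 the change form has 81 to 88% power. If 0.5 SD was meant as an SD of change, the planned power holds by construction.

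**Conclusion.** The concern holds as a matter of conditional error and lost efficiency. The planned estimate is unbiased over randomisations, so it would be wrong to call the primary analysis invalid. In the trial actually run, however, a chance baseline gap would move the t2 effect by -(1-rho) times that gap. At rho 0.5 to 0.6 this is typically 0.055 to 0.07 SD, and 0.11 to 0.14 SD at a gap of 0.28 SD, which is roughly a quarter of the 0.5 SD target. The stated rule cannot be relied on to remove it. Consistent adjustment would, and would also reduce the variance by 20 to 25%. The planned 80% power is missed only if rho is below about 0.5 and 0.5 SD is cross-sectional.

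These sizes rest on an assumed rho and on equal variances across visits. The statement that the correction changes almost nothing rests on its being a main effect.

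**What to change.** Remove the baseline tests as the trigger for adjustment; a descriptive baseline table is enough. For PAM, GSE and health-related quality of life, prespecify one baseline-adjusted mixed model, used whatever the observed balance. There are two suitable choices:

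- t0, t1 and t2 as responses with a common t0 mean in both arms (terms: time, arm x t1, arm x t2). This keeps patients who have only t0 data. With a random intercept alone it imposes one common correlation across visits.
- t1 and t2 as responses, with the baseline value and baseline x time as covariates.

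The two are not strictly equivalent when patients drop out, so the plan should name one. Any further covariates, such as cancer type, should be listed in advance, with the form in which they enter.

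The cost is a change of wording. The data, the software and the sample size stay as they are.

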#### Quality of life

Quality of life is measured by the European Organization for Research and Treatment of Cancer Quality of Life Questionnaire for cancer patients in palliative care (EORTC QLQ-C15-PAL). The EORTC QLQ-C15-PAL is an abbreviated 15-item version of the EORTC QLQ-C30 questionnaire. The EORTC QLQ-C15-PAL questionnaire is specifically designed for patients with advanced, incurable and symptomatic cancer with a median life expectancy of a few months [33].

The EORTC QLQ-C15-PAL comprises a global quality of life scale, two functional scales (physical and emotional functioning), two symptom scales (fatigue and pain), and four single items (dyspnea, insomnia, appetite loss, and constipation) [33]. All scales range in score from 0 to 100. A high score on the global quality of life scale represents a high quality of life and a high score on a functional scale represents a high or healthy level of functioning. A high score on a symptom scale indicates a high level of symptoms [34].

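### One blanket one-tailed 0.05 rule covers seven or eight moderator models and up to ten secondary scores, with no correction across them and no exploratory label

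*Protocol article*

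**What the plan says.** All of the rules are in the Statistical analyses section of the protocol article.

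- **Moderators.** "LMM will also be used to determine whether age, gender, socio-economic status (e.g. education level and work situation), cancer type", and then "treatment modality, time since treatment, and baseline quality of life moderate the efficacy of Oncokompas". That is eight variables if education level and work situation are counted separately, as the section on sociodemographic and medical data lists them. It is seven if socio-economic status is one composite.
- **Model for each moderator.** "Fixed effects will be used for study arm, time, the potential moderator, and all two-way and three-way interaction effects".
- **Error rule.** "All tests will be one-tailed", and a p-"value < 0.05 will be considered significant for all analyses".
- **Only correction named.** "Independent samples t-tests with Bonferroni correction will be used to measure the differences between the intervention group and the control group at follow-up measurements". The number of comparisons it covers is not given.
- **When that correction comes into play.** "Post-hoc analyses will be applied when significant results are found in the efficacy and moderation analyses mentioned above".

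The Outcome assessment section names one primary outcome, the PAM, and two secondary efficacy outcomes, general self-efficacy and health-related quality of life. The Quality of life section lists the QLQ-C15-PAL scores as a global scale, two functional scales, "two symptom scales (fatigue and pain), and four single items (dyspnea, insomnia, appetite loss, and constipation". The article sets no priority among these scores and does not describe the moderator or secondary analyses as exploratory.

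**The concern.** The article does not leave multiplicity open for a later document. It fixes a threshold for every analysis, and a later plan that corrected across moderators or outcomes would depart from the published rule. Applied as written, each moderator and each secondary score can be declared significant at 0.05 whatever the number tested. The Bonferroni step does not change this, because moderation or a secondary effect has already been declared by the time it is reached.

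Two features add to the problem. The trial is sized for a single main effect, so its power to detect moderation is low. And the one-tailed rule has no meaning for a test with several degrees of freedom, which is what an arm-by-time-by-moderator term becomes if the three time points are treated as categories.

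At stake is how the secondary and subgroup results can be read. The Discussion places self-efficacy and quality of life beside patient activation as efficacy outcomes, so a chance finding on one score could be reported as evidence of efficacy.

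**Working it through.** **1. The plan's own figure.** Sample size section: 0.5 SD, one-tailed alpha 0.05, power 0.80.

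- Normal approximation: 2 × (1.645 + 0.842)² / 0.5² = 49.5, so 50 per arm.
- Exact t-test: power is 0.799 at 50 per arm and 0.806 at 51, so 51 per arm is right.
- Dropout of 25%: 51 / 0.75 = 68 per arm, 136 in total.

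The stated sample size is reproduced. It rests on one outcome and one comparison.

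**2. Number of tests.**

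- Moderators: age, gender, education level, work situation, cancer type, treatment modality, time since treatment and baseline quality of life make 8, or 7 with socio-economic status as one composite.
- Secondary scores: GSE 1, plus QLQ-C15-PAL 1 + 2 + 2 + 4 = 9, giving up to 10. The article describes the nine scores but does not say that all will be tested.

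**3. Chance of at least one false positive.** With all null hypotheses true and k independent tests at 0.05, this is 1 − 0.95^k. For correlated tests, one-sided normal statistics with a common correlation were simulated. The correlations are assumptions; the article gives none.

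| Family | k | Independent | r = 0.3 | r = 0.5 | r = 0.7 |
|---|---|---|---|---|---|
| Moderators, socio-economic status as one | 7 | 30.2% | 24.5% | 20.4% | 15.8% |
| Moderators, socio-economic status as two | 8 | 33.7% | 26.7% | 21.9% | 16.8% |
| Secondary scores | 10 | 40.1% | 30.9% | 24.7% | 18.5% |

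Even the lowest value, 15.8%, is about three times the nominal 5%.

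**4. Power for moderation.** Assume a binary moderator split evenly, 51 completers per arm at one time point, and an interaction of 0.5 SD.

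- Standard error = 2 × √(2/51) = 0.396 SD.
- z = 0.5 / 0.396 = 1.26.
- One-sided 0.05: Φ(1.26 − 1.645) = 0.35.
- Two-sided 0.05: Φ(1.26 − 1.96) = 0.24.

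**5. Degrees of freedom.** The inclusion criteria list six cancer types. With time as three categories (an assumption), the three-way term has (6 − 1) × (3 − 1) = 10 degrees of freedom. If the 102 completers were spread evenly, there would be 102 / 12 = 8.5 per type per arm. A binary moderator would already give 1 × 2 = 2 degrees of freedom. Neither test has a direction, so it cannot be one-tailed.

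**The case against.** The strongest reply is that there is one primary outcome, the sample size rests on it alone, and unadjusted secondary and moderator tests beneath a single primary are common practice, with exploratory labels often left to an analysis plan. The moderators are also named in advance and tested by formal interaction terms, and the follow-up comparisons are gated and Bonferroni-corrected. Much of this stands. The primary test is not affected, and these are real safeguards. They do not answer the point, because the article states a threshold for every analysis and the correction begins only after that threshold has been passed.

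A reader might also infer stronger things that the documents do not support:

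- **That a false positive is likely.** In either family alone the chance is below one half even under independence, and positive correlation, plausible among scales of one questionnaire, lowers it.
- **That 88 tests (8 moderators on 11 scores) will give 4.4 false positives.** The article does not say that moderation is tested on every outcome; its only example is patient activation.
- **That the moderator figure is 57% (1 − 0.90^8).** This requires halving omnibus p-values, which the article nowhere proposes.
- **That a significant moderator is more likely noise than signal.** That needs a prior. At power 0.35, a significant result is more likely true once the share of real moderators exceeds 0.05 / (0.05 + 0.35) = 12.5%; at power 0.24 the share is 0.05 / (0.05 + 0.24) = 17%.
- **That moderator results would decide who is offered the application.** The Discussion speaks only of implementation if the application proves effective.

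The power figure is itself approximate: the planned mixed model can use partial data from all 136 randomised patients.

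**Conclusion.** The point holds as a material inflation of false-positive risk in the moderator and secondary analyses, produced by a rule that the article states. Its size is 30-34% across seven or eight moderators and 40% across ten secondary scores, given all nulls true, independent tests and all nine QLQ-C15-PAL scores tested. It falls to about 17-27% for eight tests and 19-31% for ten at assumed correlations of 0.3 to 0.7. Power for a plausible interaction is low, at about 0.35 one-sided or 0.24 two-sided under the assumptions shown. The one-tailed rule is also badly fixed for any interaction term with more than one degree of freedom. The primary conclusion on the PAM is untouched, so this should be corrected but does not threaten the trial's main result.

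**What to change.** Replace the blanket rule for these analyses.

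- **Moderation.** Test it on the PAM with the two-sided (omnibus) interaction test. Apply Holm across the listed moderators, having stated whether socio-economic status counts as one variable or two. Report every interaction with 95% intervals and label the set exploratory.
- **Secondary outcomes.** Treat them as supportive. Either apply Holm across the scores tested, or report them with 95% intervals and no claim of significance.
- **Post-hoc tests.** State which comparisons the Bonferroni correction covers.

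The smallest p-value would then have to be at or below 0.05/8 = 0.00625 for eight moderators (0.05/7 = 0.0071 for seven) and 0.05/10 = 0.005 for ten secondary scores.

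The cost is wording, and fewer nominally significant secondary and subgroup results. At 0.00625 two-sided, power for the interaction in the working falls to Φ(1.26 − 2.73) = 0.07, so the intervals would be the useful output. The sample size stays at 136, the primary test is unchanged, and no new data are needed.
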